### 6.5.3 VIRULENCE AND IMMUNOLOGICAL STUDIES

In prior studies, we have used patient peripheral blood mononuclear cells (PBMC) and CSF samples and linked clinical baseline and outcome data to better understand the association of systemic and site-of-infection host immune-parameters with outcomes, including survival and the development of

IRIS. Immune-active adjunctive therapies remain an important goal, given the outcomes achievable even with the best current antifungal drugs and the paucity of new drugs under development. Given the size of this phase-III trial, similar sub-studies will be developed, which will have much greater power, and add value to the main study. Exploration of differences in immune responses between patients presenting after initiating ART compared to those who are ART-naïve will help define the immunopathology of “unmasking” immune reconstitution inflammatory syndrome, and potentially guide future host-directed therapies to improve outcomes among this increasingly important patient group. Blood will also be collected for sub-studies determining how polymorphisms in immune response genes relate to susceptibility to and outcomes from cryptococcal meningitis. This work builds on earlier work from a South African cohort demonstrating polymorphisms in genes associated with intracellular pathogen processing, particularly macrophages, are associated with the development of cryptococcal infection. Samples from this large cohort will provide the power to definitively examine these associations. CSF profiling is feasible across sites, whereas PBMC collection will be restricted to smaller numbers of patients at sites with facilities for and experience in PBMC isolation (Blantyre, Harare, Gaborone, Cape Town). Of note, facilities to perform the detailed flow-cytometric analyses required for future analyses are available at several of the study sites, including Blantyre, Harare and Cape Town. Wherever materials are collected for genetic analysis this will be clearly explained on the consent form, and patients will indicate specific consent to this analysis.

Cryptococcal isolates will be collected for studies on *C. neoformans* evolution and virulence. Our prior studies have begun to define pathogen variation that impacts clinical outcome and started to give more detailed insight into *C. neoformans* evolution. These studies however have been limited in power. The large number of patients in AMBITION-cm will provide for definitive assessment of these associations. Collection and storage of all isolates is feasible and will be incorporated into this work package for future isolate whole genome sequencing, given that sequencing technologies continue to improve and costs reduce.

**Note: the sub studies will not interfere with either enrolment or the key outcomes from the main phase III trial.** Analyses will be performed at the recruiting sites or involve technology and skills transfer to the recruiting sites, and will have leadership from both African and European Partners.

## 6.6 EARLY STOPPING OF FOLLOW-UP

If a patient chooses to discontinue their trial treatment, they should always be followed up providing they are willing, that is, they should be encouraged to not leave the whole trial and agree to week 10 outcome assessment and week 16 telephonic follow-up. If they do not wish to remain on trial follow-up, however, their decision must be respected and the patient will be withdrawn from the trial completely. The trial team should be informed of this in writing using the appropriate documentation. Patients stopping early have a negative impact on a trial's data. We will ensure patients have all relevant information about the trial so that they can make an informed decision to stop or continue, as they wish.

If the medical data collected during the patient's participation in the trial are kept for research and analysis purposes, they will be fully anonymised as with all patient data. Consent for future use of stored samples already collected can be refused when leaving the trial early (but this should be discouraged and should follow a discussion).

Patients may change their minds about stopping trial follow-up at any time and re-consent to participation in the trial.

Patients who stop trial follow-up early will not be replaced.

## **6.7 PATIENT TRANSFERS**

If a patient moves from the area, every effort should be made for the patient to be followed up telephonically and for appropriate medical follow-up and treatment to be arranged locally. In Malawi patients may be transferred between sites in Lilongwe and Blantyre.

## **6.8 LOSS TO FOLLOW-UP**

Every effort will be made (for example with mobile telephone calls and financial help with travelling expenses) to obtain accurate and complete follow-up data for at least 10 weeks after the start of treatment. Follow-up will be performed according to this protocol, and outpatient follow-up will be identical in both trial arms. If a patient fails to attend out-patient clinic visits, the research nurse will visit the home address and make every effort to persuade the patient to attend and continue antifungal and antiretroviral treatment.

## **6.9 ASSESSMENTS AT TRIAL CLOSURE**

The trial will be considered closed when the last patient has completed 10 weeks' active follow-up in the study and the 16-week telephonic follow-up call, and all follow-up and laboratory reports including repeat viral load testing in ART failure cases have been received.

## SAFETY REPORTING

The principles of ICH GCP require that both investigators and sponsors follow specific procedures when notifying and reporting adverse events or reactions in clinical trials. These procedures are described in this section of the protocol. [Section 7.1 - Definitions](#) lists definitions, [Section 7.3 - Investigator Responsibilities](#) gives details of the investigator responsibilities and [Section 7.4 - Sponsor Responsibilities](#) provides information on sponsor responsibilities.

### 7.1 DEFINITIONS

The definitions of the EU Directive 2001/20/EC Article 2 based on the principles of ICH GCP apply to this trial protocol. These definitions are given in [Table 7.1: Definitions](#).

**Table 7.1: Definitions**

| TABLE                                                                                                                  | DEFINITION                                                                                                                                                                                                                                                                                                                                                                                                                                                             |
|------------------------------------------------------------------------------------------------------------------------|------------------------------------------------------------------------------------------------------------------------------------------------------------------------------------------------------------------------------------------------------------------------------------------------------------------------------------------------------------------------------------------------------------------------------------------------------------------------|
| Adverse Event (AE)                                                                                                     | Any untoward medical occurrence in a patient or clinical trial subject to whom a medicinal product has been administered including occurrences that are not necessarily caused by or related to that product.                                                                                                                                                                                                                                                          |
| Adverse Reaction (AR)                                                                                                  | Any untoward and unintended response to an investigational medicinal product related to any dose administered.                                                                                                                                                                                                                                                                                                                                                         |
| Unexpected Adverse Reaction (UAR)                                                                                      | An adverse reaction, the nature or severity of which is not consistent with the information about the medicinal product in question set out in the Summary of Product Characteristics (SPC) or Investigator Brochure (IB) for that product.                                                                                                                                                                                                                            |
| Serious Adverse Event (SAE) or Serious Adverse Reaction (SAR) or Suspected Unexpected Serious Adverse Reaction (SUSAR) | Respectively any adverse event, adverse reaction or unexpected adverse reaction that: 
 
▪ Results in death
 
▪ Is life-threatening*
 
▪ Requires hospitalisation or prolongation of existing hospitalisation**
 
▪ Results in persistent or significant disability or incapacity
 
▪ Consists of a congenital anomaly or birth defect
 
▪ Is another important medical condition***
 
 |

\*The term life-threatening in the definition of a serious event refers to an event in which the patient is at risk of death at the time of the event; it does not refer to an event that hypothetically might cause death if it were more severe, for example, a silent myocardial infarction.

\*\*Hospitalisation is defined as an inpatient admission, regardless of length of stay, even if the hospitalisation is a precautionary measure for continued observation. Hospitalisations for a pre-existing condition, that has not worsened or for an elective procedure do not constitute an SAE.

\*\*\* Medical judgement should be exercised in deciding whether an AE or AR is serious in other situations. The following should also be considered serious: important AEs or ARs that are not immediately life-threatening or do not result in death or hospitalisation but may jeopardise the subject or may require intervention to prevent one of the other outcomes listed in the definition above; for example, a secondary malignancy, an allergic bronchospasm requiring intensive emergency treatment, seizures or blood dyscrasias that do not result in hospitalisation or development of drug dependency. Presence of malaria is not an SAE unless the current infection is life threatening.

### 7.1.1 MEDICINAL PRODUCTS

An investigational medicinal product (IMP) is defined as the tested investigational medicinal product and the comparators used in the study. (EU guidance ENTR/CT 3, April 2006 revision).

Adverse reactions include any untoward or unintended response to drugs. Reactions to an IMP (i.e. L-AmB) or comparator (i.e. amphotericin B) should be reported appropriately.

### 7.1.2 ADVERSE EVENTS

Adverse Events include:

- An exacerbation of a pre-existing illness
- An increase in frequency or intensity of a pre-existing episodic event or condition
- A condition (even though it may have been present prior to the start of the trial) detected after trial drug administration
- Continuous persistent disease or a symptom present at baseline that worsens following administration of the study treatment

### 7.1.3 EXEMPTED ADVERSE EVENTS

Adverse Events do not include:

- Medical or surgical procedures; the condition that leads to the procedure is the adverse event
- Pre-existing disease or a condition present before treatment that does not worsen
- Hospitalisations where no untoward or unintended response has occurred, e.g., elective cosmetic surgery, social admissions
- Overdose of medication without signs or symptoms

### 7.1.4 DISEASE-RELATED EVENTS

Cryptococcal meningitis carries a high mortality, with an expected acute mortality of approximately 30%. All deaths will be reported as adverse events. Expected disease related morbidities such as development of visual impairment or seizures will also be reported as adverse events. The only exception to this is elevated CSF pressure, which will be routinely recorded in CRFs, and not reported as an adverse event.

### 7.1.5 OTHER STUDY-SPECIFIC REQUIREMENTS

In the event that the day 7 lumbar puncture identifies an increase in colony forming units from baseline this must be reported as an SAE. The co-ordinating centre will be responsible for managing this situation on a case-by-case basis.

## 7.2 OTHER NOTABLE EVENTS

### 7.2.1 PREGNANCY

Pregnant women will be excluded from the study. All participants will be offered appropriate contraception advice at enrolment. If a participant is found to be pregnant during the study they will

discontinue the study intervention and be treated by their attending physicians according to local guidelines. Such patients will be followed to the end of their pregnancy and pregnancy outcomes recorded.

### 7.3 INVESTIGATOR RESPONSIBILITIES

All non-serious AEs and ARs, whether expected or not, should be recorded in the patient's medical notes and reported in the appropriate section of the eCRF Follow-up Form and sent to the co-ordinating centre within the agreed timescale (as part of the monthly reports from each site). SAEs and SARs should be notified to the co-ordinating centre within 48 hours of the investigator becoming aware of the event.

#### 7.3.1 INVESTIGATOR ASSESSMENT

The chief investigators (or a delegate) will evaluate all SAEs received for seriousness, expectedness and causality. Investigator reports of SUSARs will be reviewed and those that are SUSARs identified and reported to the regulatory authorities. The causality assessment given by the local investigator cannot be overruled in the case of disagreement, but both opinions will be provided in subsequent reports.

##### 7.3.1.A Seriousness

When an AE or AR occurs, the investigator responsible for the care of the patient must first assess whether the event is serious using the definition given in [Table 7.1: Definitions](#). If the event is serious **and not only related to disease progression**, then an SAE Form must be completed and the co-ordinating centre notified within 48 hours.

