##### 7.3.1.C Causality

The investigator must assess the causality of all serious events or reactions in relation to the trial therapy using the definitions in [Table 7.2: Assigning Type of SAE Through Causality](#). There are five categories: unrelated, unlikely, possible, probable, and definitely related. If the causality assessment is unrelated or unlikely to be related, the event is classified as an SAE. If the causality is assessed as possible, probable or definitely related, then the event is classified as an SAR.

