#### 7.3.1.E Notification

The co-ordinating centre should be notified of all SAEs within 24 hours of the investigator becoming aware of the event.

Investigators should notify the co-ordinating centre of all SAEs occurring from the time of randomisation until 30 days after the last protocol treatment administration. SARs and SUSARs must be notified to the co-ordinating centre until trial closure.

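### Section 7.3.1.A exempts serious disease-only events from the SAE form and notification, while 7.3, 7.3.1.E and the front-page SAE box require it for every SAE

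*Protocol*

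**What the plan says.** Section 7.3.1.A has the investigator first judge seriousness against Table 7.1. It then requires an SAE form, and notification within 48 hours, if the event is serious "and not only related to disease progression".

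Other current rules on notification contain no such condition:
- Section 7.3: "SAEs and SARs should be notified to the co-ordinating centre within 48 hours of the investigator becoming aware of the event".
- Section 7.3.1.E: "The co-ordinating centre should be notified of all SAEs within 24 hours of the investigator becoming aware of the event". It then repeats the duty for all SAEs from randomisation until 30 days after the last protocol treatment.
- The SAE reporting box at the front of the protocol asks for a completed form within 24 hours for any SAE.

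On classification, Table 7.1 defines an SAE by its outcome, whatever the cause, and 7.3.1.C states: "If the causality assessment is unrelated or unlikely to be related, the event is classified as an SAE". In Table 7.2 an event with another reasonable explanation, such as the patient's own condition, is an unrelated SAE.

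On disease-related events, 7.1.4 has all deaths reported as adverse events and adds: "Expected disease related morbidities such as development of visual impairment or seizures will also be reported as adverse events". It continues: "The only exception to this is elevated CSF pressure, which will be routinely recorded in CRFs, and not reported as an adverse event".

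On central review, 7.3.1 says: "The chief investigators (or a delegate) will evaluate all SAEs received for seriousness, expectedness and causality". Section 7.4 likewise has medically qualified staff review the SAE reports that are received.

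**The concern.** For a serious event that the investigator attributes to meningitis alone, the answer to a basic question (does this need an SAE form?) depends on which section the site reads. Two sites could both act in good faith and produce different SAE counts. Because 7.4 as worded puts fatal and life-threatening SAEs on a 7-day clock to the authorities, they could also generate different regulatory reports.

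What is at stake is the second look. An event withheld under 7.3.1.A is not among those received, so the judgement that it was disease only rests with an investigator who knows the arm (4.2, 9.1). That judgement is sensitive here because lack of efficacy of a shortened regimen would present as disease progression, and section 1.5 names inferiority of the new regimen as a risk to participants. The issue bears mainly on non-fatal deterioration, since deaths are recorded in any case (6.2).

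**Working it through.** No arithmetic settles this. The check sets the rules side by side for one case: a serious event due only to meningitis, occurring inside the 7.3.1.E window.

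| Place | Treatment of the event | Deadline |
|---|---|---|
| Front SAE box | form required | 24 h |
| 7.3 | notify | 48 h |
| 7.3.1.A | no form, no notification | none (48 h for other serious events) |
| 7.3.1.E | notify | 24 h |
| Table 7.1 | is an SAE, by outcome | not stated |
| 7.3.1.C, Table 7.2 | is an unrelated SAE | not stated |
| 7.1.4 | reported as an adverse event | not stated |

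1. *Is the event an SAE?* Yes. Table 7.1 does not depend on cause, and Table 7.2 has a category for events explained by the patient's condition.
2. *Must it be notified?* Yes under the front box, 7.3 and 7.3.1.E; no under 7.3.1.A. This is the direct contradiction. With Table 7.1 and 7.3.1.C the conflict is by implication: they make the event an SAE but do not mention the form.
3. *Does another section resolve it?* No. Nothing in 7.3 or 7.3.1.E defers to 7.3.1.A, and the protocol does not define when an event is only disease progression.
4. *What route remains for an exempted event?* None is stated. The eCRF Follow-up Form and monthly report in 7.3 are for non-serious events.
5. *Who reviews it?* The reviews in 7.3.1 and 7.4 cover what is received, so they do not cover an event withheld under 7.3.1.A.

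**Example.** The Table 7.1 footnote, which leaves room for medical judgement, offers "seizures or blood dyscrasias that do not result in hospitalisation or development of drug dependency" among its examples of events that may count as serious. Section 7.1.4 names seizures as expected disease morbidity. A seizure judged serious and due only to meningitis needs notification within 24 hours under 7.3.1.E and none under 7.3.1.A.

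**Day-7 rise in colony counts.** Sections 6.3 and 7.1.5 make this a mandatory SAE although it may be a sign of disease progression. The mandatory wording is best read as governing, but 7.3.1.A does not say so.

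**Size.** The protocol gives neither the share of serious events that would be judged disease only nor the number of non-fatal serious events. No count of withheld reports follows from it.

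**The case against.** The strongest reply is that the exemption is deliberate. It is emphasised in the text, it is the specific rule in the sequence A to E, and in a disease with about 30% expected acute mortality (7.1.4) it is defensible not to ask for an SAE form for every disease event. On that view 7.3.1.E only sets the deadline and window for events that pass A. The intention is plausible, but the reading does not rescue the text. Section 7.3.1.E speaks of all SAEs without reference to A, 7.3 and the front box say the same, and an exempted serious event is left with no form or deadline.

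Other parts of the reply stand:
- Section 7.1.4 is not in contradiction. It concerns reporting as adverse events, its exception for raised CSF pressure is an exception to that, and it can be obeyed together with 7.3.1.A.
- A reader might infer that exempted events go entirely unchecked. The documents do not support this. Co-ordinating centre staff review eCRF data (8.2), the IDMC reviews side effects and mortality (6.3), and grade III/IV events are tabulated by arm (9.5). What is lost is the SAE-level review of seriousness, causality and expectedness, and that review adds a second opinion without overruling the local one.
- Non-response has its own safeguards: clinic review, CSF cultures and rescue therapy (1.5), and the day-7 rule.

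**Conclusion.** The contradiction is real and in current text. It is direct between 7.3.1.A on one side and 7.3, 7.3.1.E and the front SAE box on the other, and by implication with Table 7.1 and 7.3.1.C with Table 7.2. A stated safety-reporting rule cannot be followed as written, so it should be corrected. It is not a threat to the trial's main result: the primary endpoint, the IDMC's mortality review and the planned grade III/IV tabulation do not depend on SAE forms.

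The size cannot be derived. A reader might take the expected deaths as its measure: 0.30 × 850 = 255 at the acute mortality in 7.1.4, or 0.35 × 850 = 297.5, about 298, at the 10-week mortality in 9.3. These figures do not size the loss. Deaths are captured as outcome data whichever section a site follows, the disease-only share could be anything from none to all, and the events that matter most here are non-fatal. Nor do the documents show that the two arms would be affected differently. The conclusion rests only on the wording of the sections compared.

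**What to change.** Preferred change, in one amendment:
- **7.3.1.A:** delete the exemption, so that every serious event gets an SAE eCRF and is notified as in 7.3.1.E. Record disease progression alone as an unrelated SAE in the terms of Table 7.2.
- **7.3 and 7.3.1.A:** change 48 hours to 24 hours, to agree with 7.3.1.E and the front box. Otherwise sites would still face two deadlines.
- **7.4:** state that the 7-day report to authorities applies to fatal and life-threatening SUSARs, and to other SAEs only as local rules require. Without this, each expected death reported as an SAE would also fall under expedited reporting.

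If the exemption is intended, state it in 7.3 and 7.3.1.E as well (the front box should then agree). Give a closed list of exempt events, say that 7.1.5 always overrides it, and require exempt serious events on a dated eCRF page within 24 hours, tabulated by arm for the IDMC.

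Cost: more SAE forms at sites that have been following 7.3.1.A, although 7.3.1.E already requires them, and a protocol amendment that each ethics committee must approve (11.2.2). No new visit or test is needed.
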